# Effects of naringenin supplementation in overweight/obese patients with non-alcoholic fatty liver disease: study protocol for a randomized double-blind clinical trial

**DOI:** 10.1186/s13063-021-05784-7

**Published:** 2021-11-13

**Keywords:** Non-alcoholic-fatty liver disease, Naringenin, Metabolic parameters, Adiponectin, Neuregulin-4

## Abstract

**Introduction:**

Non-alcoholic fatty liver disease (NAFLD) is one of the main causes of chronic liver disease worldwide. Flavonoids, a group of natural compounds, have garnered a great deal of attention in the management of NAFLD because of their profitable effects on glucose and lipid metabolism, inflammation, and oxidative stress which are the pivotal pathophysiological pathways in NAFLD. Naringenin is a citrus-derived flavonoid with a broad spectrum of potential biological effects including anti-inflammatory and antioxidant properties, which may exert protective effects against NAFLD. The present clinical trial aims to examine the efficacy of naringenin supplementation on plasma adiponectin and neurogulin-4 (NRG-4) concentrations, metabolic parameters, and liver function indices in overweight/obese patients with NAFLD.

**Methods and analysis:**

This is a double-blind, randomized, placebo-controlled clinical study that will investigate the impacts of naringenin supplementation in overweight/obese patients with NAFLD. Liver ultrasonography will be applied to diagnose NAFLD. Forty-four eligible overweight/obese subjects with NAFLD will be selected and randomly assigned to receive naringenin capsules or identical placebo (each capsule contains 100 mg of naringenin or cellulose), twice daily for 4 weeks. Participants will be asked to remain on their usual diet and physical activity. Safety of naringenin supplementation was confirmed by the study pharmacist. The primary outcome of this study is changes in adiponectin circulating levels. The secondary outcomes include changes in NRG-4 levels, liver function indices, metabolic parameters, body weight, body mass index (BMI), waist circumference (WC), blood pressure, and hematological parameters. Statistical analysis will be conducted using the SPSS software (version 25), and *P* value less than 0.05 will be regarded as statistically significant.

**Discussion:**

We hypothesize that naringenin administration may be useful for treating NAFLD by modulating energy balance, glucose and lipid metabolism, oxidative stress, and inflammation through different mechanisms. The current trial will exhibit the effects of naringenin, whether negative or positive, on NAFLD status.

**Ethical aspects:**

The current trial received approval from the Medical Ethics Committee of Tehran University of Medical Sciences, Tehran, Iran (IR.TUMS.MEDICNE.REC.1399.439).

**Trial registration:**

Iranian Registry of Clinical Trials IRCT201311250155336N12. Registered on 6 June 2020

**Supplementary Information:**

The online version contains supplementary material available at 10.1186/s13063-021-05784-7.

## Introduction

Non-alcoholic fatty liver disease (NAFLD), defined as the accumulation of triglycerides within hepatocytes that exceeds 5% of liver weight, is an umbrella word for a broad spectrum of liver abnormalities including non-alcoholic steatohepatitis (NASH), advanced *fibrosis*, cirrhosis, and hepatocellular carcinoma (HCC) [1, 2]. Based on epidemiological evidence, the current global prevalence rate of NAFLD is 25% [3]. Different kinds of methods including platelet count, serum aminotransferase levels, the fibrosis-4 (FIB-4) index, NAFLD fibrosis score (NAS), imaging techniques, ultrasonography, and liver biopsy are used for the diagnosis of NAFLD. Despite the invasive nature of liver biopsy, it remains the gold standard to define and diagnose the severity of NAFLD [4]. However, ultrasonography can determine moderate and severe liver steatosis with an acceptable accuracy. A meta-analysis performed by Hernaez et al. [5] reported that sensitivity and specificity of ultrasonography were 84/8% and 93/6%, respectively. Experts are currently ongoing to rename NAFLD as metabolic-associated fatty liver disease (MAFLD) because of the close relationship between fatty liver and metabolic disorders [6]. Emerging evidence suggests that there is a bidirectional association between NAFLD and its risk factors including obesity, insulin resistance, dyslipidemia, oxidative stress, and inflammation [7]. Adipose tissue secretes a wide variety of bioactive substances, known as adipokines, which dysregulated secretion of these factors is involved in the development of NAFLD. Adiponectin and neuregulins are proposed to be linked with NAFLD [8]. Adiponectin, as an anti-inflammatory adipokine, is known to be inversely associated with insulin resistance, lipid accumulation, and NAFLD by playing a pivotal role in the modulation of hepatic glucose and lipid metabolism, stimulating the AMP-activated protein kinase (AMPK) signaling pathway, and decreasing the expression of peroxisome proliferator-activated receptor-α (PPAR-α) in the liver [9]. Regarding neuregulin-4 (NRG-4), a novel brown adipose tissue (BAT)-secreted adipokine, a growing body of evidence has demonstrated that it may protect metabolic hemostasis by regulating glucose and lipid metabolism. Also, hepatic de novo lipogenesis was controlled by BAT through NRG-4 [10]. In addition, NRG-4 transgenic mice had less lipid accumulation in the liver compared to the control mice [11].

It has become clear that diet, mainly dietary patterns, has a pivotal role in the progression of a wide range of liver conditions including NAFLD, NASH, fibrosis, and cirrhosis [12]. The most recent confirmed hypothesis explaining the pathogenesis of NAFLD is the multiple-hit theory which suggests multiple factors including insulin resistance, nutritional factors, gut microbiota, adipose tissue-secreted hormones, and genetic and epigenetic factors concurrently contribute to the induction of NAFLD in genetically predisposed individuals [13]. Although there are no approved pharmacological agents for the treatment of NAFLD, some dietary supplements including silymarin, omega-3, vitamin E, vitamin D, coenzyme Q10, and flavonoids can improve liver function indices in NAFLD patients [14]. Both animal and human studies have proposed that flavonoids exert protective activities against NAFLD by attenuation of nuclear factor kB (NF-kB) signaling, elevation of fatty acid oxidation in liver cells, and improvement of insulin sensitivity [15]. Among citrus-derived flavonoids, naringenin is a bitter flavanone which is mainly present in grapefruit and possesses incredible biological properties including antiviral, antioxidant, anti-inflammatory, anti-cancer, anti-hyperlipidemic, anti-hyperglycemic, and weight-lowering activities [16]. Since NAFLD is strongly related to obesity, metabolic parameters, inflammation, and oxidative stress, it seems that naringenin administration would lead to an improvement of liver indices in NAFLD patients through modulating energy hemostasis, increasing fatty acid oxidation, regulating glucose metabolism, inhibiting the expression of pro-inflammatory and pro-fibrotic signaling pathways, and attenuating oxidative stress [17]. It should be noted that consumption of most of the flavonoids like naringenin caused no side effects due to their low bioavailability and rapid metabolism and elimination [18–20]. As far as we know, no clinical trial has evaluated the effects of naringenin in NAFLD patients, yet. A recent study performed by Ahmed et al. [21] found that administration of naringenin (20 mg/kg for 4 weeks) resulted in a significant reduction in aminotransferase, total bilirubin, and levels of inflammatory biomarkers; downregulation of hepatic proapoptotic proteins; and upregulation of hepatic anti-apoptotic proteins in Wistar rats with liver injury. Moreover, an in vivo study by Chen et al. [22] concluded that naringenin and nano-naringenin administration (100 mg/kg and 25 mg/kg for 1 week, respectively) reduced serum aminotransferase levels and lipid accumulation in the liver of mice fed methionine choline-deficient diet. Furthermore, another study investigating the effects of naringenin on isoniazid- and rifampicin-induced apoptosis in hepatic injury demonstrated an improvement in anti-apoptotic effects, liver indices, and liver antioxidant content by naringenin supplementation (100 mg/kg for 2 weeks) [23]. The present clinical study aims to assess the effects of naringenin administration on plasma adiponectin concentrations in overweight/obese patients with NAFLD as the primary objective. Moreover, secondary objectives of this research include evaluating alterations in plasma NRG-4 concentrations, metabolic parameters, indices of liver function, body weight, BMI, WC, blood pressure, and hematological parameters.

## Methods and analysis

### Study design

The present research, a placebo-controlled, randomized, double-blind clinical trial examining the impacts of naringenin administration in overweight/obese NAFLD patients, is registered at the Iranian Registry of Clinical Trials (ID: IRCT20131125015536N12). This trial will be performed at the National Iranian Oil Company (NIOC) central hospital, Tehran, Iran. Written informed consent will be obtained from participants before participation in the research project by researchers. We developed the study protocol based on the Standard Protocol Items: Recommendations for Interventional Trials (SPIRIT) 2013 checklist (supplemental file 1). The timeline of the trial and study flow chart of enrollment, allocation, intervention, and assessment are presented in Table 1 and Fig. 1, respectively. Any amendments of the present study protocol which are related to safety and benefit of patients and the protocol deviations and unintentional alterations in study protocol that do not affect subject’s rights, study’s risk or benefit, the integrity of data, and safety or welfare, will require to be confirmed by the Department of Clinical Nutrition and Medical Ethics Committee of Tehran University of Medical Sciences, Tehran, Iran, before the study conduction. Any alteration in the study protocol will be sent to the *Trials* journal (www.trialsjournal.biomedcentral.com).

**Table 1 Tab1:** Timeline of the trial

Explanation of the trial activities	Time (months)															
	1	2	3	4	5	6	7	8	9	10	11	12	13	14	15	16
Material preparation	*	*	*	*												
Recruitment					*	*	*	*								
Clinical assessments at baseline					*	*	*	*								
Nutritional assessments at baseline					*	*	*	*								
Biochemical assessments at baseline					*	*	*	*								
Hepatic steatosis and fibrosis assessments at baseline					*	*	*	*								
Intervention									*	*	*	*	*			
Clinical assessments after intervention									*	*	*	*	*			
Nutritional assessments after intervention									*	*	*	*	*			
Biochemical assessments after intervention									*	*	*	*	*			
Hepatic steatosis and fibrosis assessments after intervention									*	*	*	*	*			
Data analysis														*	*	
Writing the final report of the trial																*
The expected time	*	*	*	*	*	*	*	*	*	*	*	*	*	*	*	*

**Fig. 1 Fig1:**
[figure not shown]
Study flowchart. BMI, body mass index; NAFLD, non-alcoholic fatty liver disease

### Study setting

The current research will be performed at the NIOC central hospital, Tehran, Iran, and participants will be selected from NAFLD patients who are newly diagnosed by an expert radiologist using ultrasonography.

### Study participants and enrollment

NAFLD patients will be recruited from the clients of the NIOC central hospital ultrasound department by two independent researchers. It should be noted that due to the simultaneous coronavirus disease 2019 (COVID-19) pandemic and the implementation of the current study, researchers should expand their presence time in NIOC central hospital ultrasound department for achieving adequate participant enrollment to reach the target sample size. An adept radiologist with sufficient expertise in the diagnosis of fatty liver through ultrasonography will diagnose patients with NAFLD. Patients that satisfy the following inclusion criteria will be eligible to participate in this research project.

#### Inclusion criteria

The inclusion criteria are considered as follows: individuals aged between 20 and 65 years, subjects whose BMI ranged between 25 and 35 kg/m^2^, diagnosis of NAFLD by a specialist based on ultrasonography results, and patients who fill out a written informed consent for participation in this study. To ensure minimal loss to follow-up, we will include patients who live in Tehran.

#### Exclusion criteria

The exclusion criteria will include subjects who are pregnant or breastfeeding or menopause; who are afflicted by diabetes mellitus, hypertension, human immunodeficiency virus, gastrointestinal diseases, organs failure, thyroid abnormalities, kidney disorders, autoimmune diseases, severe mental illnesses, and different kinds of malignancies; patients who had cardiovascular accidents in the last 3 months; professional athlete; and individuals who are addicted to drugs and alcohol. In addition, subjects who regularly consumed herbal essences such as silymarin, antioxidants, omega-3, probiotics, multivitamin-mineral supplements, NSAIDS, antibiotics, corticosteroids, anti-hypertension, anti-hyperglycemic, and weight-lowering agents in the last 3 months will be excluded. We will also exclude patients with pathological liver conditions including cirrhosis, virus-related hepatitis, and liver transplantation. To ensure minimal loss to follow-up, we will exclude participants who do not live in Tehran. Also, patients who are unwilling to continue collaborating on the research and have poor compliance (less than 90%) with the assigned intervention will be withdrawn from follow-up.

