### Study interventions

Forty-four eligible NAFLD patients will be randomly allocated to placebo (*n* = 22) and intervention groups (*n* = 22). Naringenin capsules (contain 100 mg naringenin) and identical placebo capsules (contain 100 mg cellulose) will be respectively administered to patients in the intervention and control groups twice a day, before lunch and dinner, for 4 weeks. Naringenin and placebo capsules will be similar in weight, size, shape, taste, color, odor, and lot number. Participants will be informed how to use their supplements, and they will be followed by phone calls once a week. Also, due to ethical considerations, physical activity and dietary recommendations will be provided by the researchers in order to improve participants’ lifestyles in both naringenin and placebo groups. No specialized diet or physical activity plan will be provided for study patients.

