### Sample size calculation

By consideration of a type I error of 5% (*α* = 0.05), a power of 90%, assumptions in the control group of 0.99, and the expected treatment effects of 0.93, according to the mean plasma levels of adiponectin as a primary outcome [28], the sample size was computed to be 21 for each group based on the two-sided *t* test. To compensate for an approximate drop-out rate of 5% during the study period, we elevate the final sample size to 22 subjects in each group.

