### Data management and monitoring

A clinical trial monitor occasionally supervises the study progress; ensures patient rights and well-being are safeguarded; the protocol, ethical requirements, standards, and regulations are being followed; the essential documentation is available; and collected data are accurate as there were recorded. One of the investigators will check the coding, security, and storage of the data. In addition, he/she will evaluate the data entry and data values twice. If any participant reports the occurrence of adverse events, more information is required to make a decision about excluding the participants from the trial. Unblinding is permissible in this situation based on the Medical Ethics Committee criteria.

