### Adherence to the intervention

The study progress will be pursued by calling the patients once a week to ensure that they regularly consume the capsules. Adherence to the intervention will be checked by counting the returned capsules at the half and end of the trial visits. The compliance rate will be computed according to the following formula, and poor compliance will be considered as less than 90% [30].
$$ \mathrm{Compliance}\ \mathrm{rate}:\left(\mathrm{capsules}\ \mathrm{taken}/\mathrm{capsules}\ \mathrm{prescribed}\right)\times 100 $$

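### Ending follow-up when capsule compliance is below 90% can leave randomised patients without a primary outcome value and turn the comparison into one among compliers

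*Protocol article*

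**What the plan says.** Under Exclusion criteria, the article states that patients who do not wish to go on with the study and "have poor compliance (less than 90%) with the assigned intervention will be withdrawn from follow-up". The rule sits among the entry criteria, but compliance with an assigned intervention exists only after allocation.

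Adherence to the intervention repeats the threshold and says when it is measured: "Adherence to the intervention will be checked by counting the returned capsules at the half and end of the trial visits". Study interventions sets the course at one capsule "twice a day, before lunch and dinner, for 4 weeks". Biochemical measurements has adiponectin measured before and after the intervention, with no sample in between. Outcomes names the change in adiponectin as primary, and Statistical analysis compares the arms at the end of the trial by ANCOVA.

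Two other passages bear on the point. In Safety evaluation, patients whose adverse events are judged related to naringenin are asked to stop it. In Data management and monitoring, after a reported adverse event, "more information is required to make a decision about excluding the participants from the trial".

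Sample size calculation goes from 21 to 22 per group "To compensate for an approximate drop-out rate of 5% during the study period".

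**The concern.** Randomisation makes the two arms comparable as they were allocated. A rule that stops measuring patients because of what they do after allocation can undo that. Capsule-taking may depend on tolerability, on adverse events or on perceived benefit, and each of these may differ between naringenin and placebo. If so, the patients left with an end-of-trial value are a selected group in each arm, and the estimate describes compliers rather than everyone allocated to naringenin.

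A later analysis plan cannot repair this. The choice of analysis set can properly wait for that plan, but a blood sample never taken cannot be restored by it. For a patient withdrawn at the mid-trial count, the missing primary outcome could only be imputed, with baseline as the only adiponectin value. With 22 patients per arm, a few such removals carry weight.

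A lesser question is whether the drop-out allowance was set with these withdrawals in mind.

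**Working it through.** **1. How easily the threshold is met.** Inputs: two capsules a day for 4 weeks (Study interventions) and a 90% limit (Adherence to the intervention).

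- Full course: 2 × 28 = 56 capsules, and 0.90 × 56 = 50.4. Five missed gives 51/56 = 91.1%, above the limit. Six missed gives 50/56 = 89.3%, below it. Six capsules are three days of treatment.
- First half, if the rule is applied to the capsules due by then and the visit falls at two weeks: 2 × 14 = 28. Two missed gives 26/28 = 92.9%; three missed gives 25/28 = 89.3%, below the limit.

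**2. Which withdrawals lose the primary outcome.** Found below 90% at mid-trial and withdrawn: there is a baseline sample and no post-intervention sample, so the change in adiponectin does not exist. First found below 90% at the final visit: the end sample may already have been drawn, so the value may exist. The first case is the clear loss.

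**3. The plan's own allowance.** Inputs: 21 evaluable per group and about 5% drop-out (Sample size calculation). 21/0.95 = 22.1, stated as 22, and 22 × 0.95 = 20.9. The figure is reproduced to rounding. The allowance is 22 − 21 = 1 patient per group (1/22 = 4.5%). Even at a true total loss of exactly 5%, the chance that a given group loses two or more of 22 is 1 − 0.95^22 − 22 × 0.05 × 0.95^21 = 1 − 0.324 − 0.375 = 30%.

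**4. Power.** The roles of 0.99 and 0.93 in the calculation are not defined, so I used the standardised effect that 21 per group and 90% power imply in a two-sided 5% t test: d = 1.025. Power comes from the non-central t distribution with non-centrality d × √(n/2) and 2n − 2 degrees of freedom.

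| Evaluable per group | Power |
|---|---|
| 21 | 90.0% |
| 20 | 88.5% |
| 18 | 84.8% |
| 16 | 80.1% |

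The article gives no non-compliance rate. Assume that compliance withdrawals come on top of the 5% drop-out, at the same rate in both arms. The number left is 22 × 0.95 × (1 − rate):

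| Further withdrawals (assumed) | Left per group | Power (normal approximation, d = 1.00) |
|---|---|---|
| 5% | 19.9 | 88% |
| 10% | 18.8 | 87% |
| 15% | 17.8 | 85% |
| 20% | 16.7 | 82% |

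**5. Selection bias, for illustration.** This is a separate scenario, with removals in one arm only. Suppose a fraction q of that arm is removed, and those patients average s standard deviations below the mean of the whole arm. The mean of the retained patients is then too high by q × s/(1 − q). With s = 0.8 (assumed), q = 0.15 gives 0.12/0.85 = 0.14 SD, and q = 0.20 gives 0.16/0.80 = 0.20 SD. If 0.8 SD is the gap to the retained patients instead, the bias is q × s = 0.12 to 0.16 SD. Neither s nor q has a source in the article. Unlike lost power, this bias does not shrink with a larger sample.

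**The case against.** The strongest objection is the wording. The sentence joins unwillingness to continue and poor compliance with an *and*. Read strictly, both are required, and the rule then reaches only people who are already leaving. That reading is possible. But the adherence section says that "poor compliance will be considered as less than 90" per cent, which makes it a category in its own right, so a list of two reasons is the more natural reading. The ambiguity itself needs correcting.

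A reader might infer that the 5% allowance is broken. The article does not support that: it gives no non-compliance rate, and the 5% may have been meant to include these withdrawals. Recruitment limited to Tehran, weekly calls and a short course also work to keep losses low. What stands is that the two sections are not linked.

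A reader might also infer that loss will differ by arm. This is possible but not shown. The capsules are matched, participants and investigators are blinded, and the Introduction expects no side effects. Nor is the adverse-event passage a fixed exclusion rule; it leaves the decision open. Still, stopping capsules after an adverse event would lower the compliance rate if the prescribed number is unchanged, so a treatment-related route into the rule exists.

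Finally, an article may leave the analysis population to another document, so its absence is not held against the plan here. That defence does not reach a rule on whom to stop measuring.

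**Conclusion.** The point holds in a limited form. The article states a rule, based on behaviour after randomisation, that on its natural reading ends follow-up for a low capsule count. Applied at mid-trial, it leaves the primary outcome unmeasured, and the end-of-trial comparison can become one among compliers without the protection of randomisation.

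The trigger is small: six of 56 capsules, or three of 28 at the half visit. How many patients it would remove is unknown. Under an assumed 15% on top of 5% drop-out, about 18 per arm remain and power is about 85% against the planned 90%. That cost is modest and secondary. The main issue is the risk of selection bias, whose direction and size the documents do not settle; the 0.12 to 0.20 SD above rests wholly on assumed inputs. The allowance of one patient per arm is not shown to cover the rule, which is less than saying that it fails.

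**What to change.** - Remove poor compliance as a reason to end follow-up, which also settles the ambiguous sentence.
- Take the end-of-trial measurements and blood sample from every randomised patient who has not withdrawn consent, whatever the capsule count and whether or not capsules were stopped.
- Make the as-randomised comparison primary, and report the set with at least 90% compliance only as a sensitivity analysis.
- State what the 5% allowance covers. If compliance no longer ends follow-up, the rule adds no loss and the stated 22 per group need not rise on its account.

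The cost is a change of wording and a few end-of-trial visits and assays for patients already enrolled. The estimate may be slightly diluted by non-compliers. Patients already measured at the final visit can be included at once; any withdrawn earlier should be counted and reported by arm. The change concerns measurement and analysis only and alters neither dosing nor any rule on stopping capsules.
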